## Data analyses

### Quantitative data (SPIRIT point 20a; 20b)

The analysis of quantitative data involves three steps.A number of scales were developed to measure HCWs’ internal and external stigma towards HIV and TB. As a method for theory testing, the scales were validated through confirmatory factor analysis (CFA) using Mplus [43]A detailed description of the validation of the scales has been published [21], but to summarise:The questionnaire items designed to measure HIV and TB stigma and which held a sufficient factor loading (> 0.5) were included in the scales, as they reflected the theoretical construct [44, 45]. Further, to test how the constructed scales fit the data using model fit indices (the comparative fit index (CFI), the Root Mean Square Error of Approximation (RMSEA), and the Standardised Root Mean Square Residual (SRMR)). A scale was considered reliable if it had a Cronbach’s alpha of above 0.7 [46]. Since the HCWs belong to very different professional categories, measurement invariance was tested among these groups when comparisons in effects or means were done. To compare regression coefficients between the groups, the meaning of the measurement (i.e. the factor loadings) must be invariant across groups; this is referred to as metric invariance. To compare stigma levels, the factor means and intercepts also need to be invariant, this is referred to as scalar invariance [47, 48].The baseline data were further analysed with different SEM models, since they could integrate the latent stigma scales. Factors associated with HIV and TB stigma were explored. In terms of a primary (measurement) outcome—scientific information was generated on the extent and sources of HIV- and TB-related stigma among HCWs in the Free State. It is important to note, for reasons explained later, in the section on ‘Monitoring’, these measurement results must be read with caution.Analyses of data in terms of the secondary (intervention) outcome—the environment in with HCW’s seek care—is ongoing. So far, two articles have been submitted. In one, a model confirmed the hypothesis that higher stigma levels among HCWs are associated with lower use of occupational health units for HIV and TB services. In another, binominal logistic regression was used to explore factors associated with HCWs’ fear of contracting TB and HIV in the workplaceWhen the post-intervention data have been gathered, the second step of the analysis will be to apply linear mixed modelling to analyse changes in HIV and TB stigma between the intervention and the control group. The within-subject correlation between the two time points can then be accounted for by introducing a random effect into the model [49]. The stigma measurements will have to be metric invariant between the intervention and the control group and scalar invariant between the different time points (pre- and post-assessment) [46, 47]SEM will allow us to test path models that optimally reflect the complex interrelationships between our different key concepts and the HIV and TB stigma between HCWs in the healthcare setting [43]. Therefore, in addition to estimating the intervention effects, the complex pathways to what might cause the effects can be explored through path and mediation analysis. These methods can also assess whether a reduction in stigma over time also could influence the secondary outcomes

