#### Sampling (SPIRIT point 14)

The parameters used for sample size calculation were estimated from the Stigma Score Pilot Study. The mean stigma score considered for the control group was 0.85 with a standard deviation of 0.71. The stigma score is expected to be reduced by approximately 24% to 0.65 in the intervention group with a standard deviation of 0.39. The two-tailed test is considered with Type I error of 0.05 and Type II error of 0.10, to give 90% power. The coefficient of variation considered for each group is 0.25 and the intra-cluster correlation coefficient is 0.05. The estimated sample size per arm is 173 and the estimated inflation factor (design effect) is 1.7. Therefore, the required sample size for this study per arm is approximately 173 × 1.7 ≈ 292 participants. The total number of participants required for this study is 584 (347 respondents in intervention sites and 237 in control sites).

The same HCWs participate in baseline and the post-intervention surveys. Based on our extensive experience of fieldwork in Free State hospitals [32], we estimate that the baseline survey will need 50% oversampling of respondents to allow for loss-to-follow up between baseline and post-intervention surveys (SPIRIT point 15). In practice, a random sample of 882 HCWs was drawn from three broad job categories: *healthcare professionals* (446) (physicians, nurses, and allied HCWs such as psychologists, pharmacists, etc.); *management and administrative staff* (116); and *support staff* (318) (e.g. messengers, cleaners, porters, housekeeping, catering, security, etc.). Two respondents did not indicate their job category.

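### The article counts equal factor means as part of scalar invariance, then makes scalar invariance over time a condition for comparing change in stigma

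*Protocol article*

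**What the plan says.** All the relevant text is in the protocol article, Data analyses, Quantitative data (SPIRIT point 20a; 20b).

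- Metric invariance, needed to compare regression coefficients: "the meaning of the measurement (i.e. the factor loadings) must be invariant across groups; this is referred to as metric invariance".
- Scalar invariance, needed to compare levels: "To compare stigma levels, the factor means and intercepts also need to be invariant, this is referred to as scalar invariance".
- The trial analysis is to "apply linear mixed modelling to analyse changes in HIV and TB stigma between the intervention and the control group".
- The condition set on that analysis: "The stigma measurements will have to be metric invariant between the intervention and the control group and scalar invariant between the different time points".

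The article gives no other definition of scalar invariance. It does not say whether invariance over time is tested in each arm or with the arms pooled.

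The planned effect is in Sampling (SPIRIT point 14): "The mean stigma score considered for the control group was 0.85 with a standard deviation of 0.71", expected to be "reduced by approximately 24% to 0.65 in the intervention group with a standard deviation of 0.39".

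**The concern.** A scalar model holds loadings and item intercepts equal, so that a difference in observed item means can be attributed to the factor mean. The factor means must therefore be free. If they are held equal as well, levels may be compared only where they do not differ.

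The article attaches this definition to the step that matters most. Change in stigma from baseline to follow-up is named under the primary outcomes, and scalar invariance between the two surveys is a stated precondition for analysing it. An analyst who followed the wording would find that the precondition fails in the situation the trial hopes to produce, a fall in stigma, and would have to stop or improvise. Either choice would be made after seeing data that reflect the result.

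**Working it through.** **1. Planned effect.** Inputs from Sampling (SPIRIT point 14): means 0.85 and 0.65, SDs 0.71 and 0.39, two-sided alpha 0.05, power 90%.

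- Check of the article's own figure: n = (0.71² + 0.39²)(1.960 + 1.282)² / 0.20² = 172.4, rounded up to 173. This matches the stated unadjusted size per arm.
- Average SD = √[(0.71² + 0.39²)/2] = 0.573. Standardised difference = 0.20/0.573 = 0.349. On the control SD alone it is 0.20/0.71 = 0.28.

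**2. What the worded condition tests.** In a one-factor model, the mean of an item at time t is intercept + loading × factor mean at t. If loadings, intercepts and factor means are all equal over time, every item mean is equal over time. The condition as worded is therefore a test that no item mean changed.

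**3. How often it fails when stigma falls as planned.** Assumptions not in the article: 5 items, loadings 0.7, residual variance 0.51, latent correlation over time 0.5, residual correlation over time 0.2, no clustering, a true latent change of −0.349 SD, and no change in how items are answered.

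- Change in each item mean: 0.7 × 0.349 = 0.2444.
- Covariance of the item change scores: diagonal part 2 × 0.51 × (1 − 0.2) = 0.816, plus a common part 0.49 × 2 × (1 − 0.5) = 0.49.
- Population misfit F = ln[1 + 5 × 0.2444² / (0.816 + 5 × 0.49)] = ln(1.0915) = 0.0875.
- Noncentrality = N × F. The standard condition has 4 degrees of freedom in the means (10 item means less 5 intercepts and 1 factor mean). The worded one has 5.

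| Case | Noncentrality | Rejected, as worded | Rejected, standard scalar |
|---|---|---|---|
| One arm, N = 237 | 20.7 | 96% | 5% |
| One arm, N = 292 | 25.6 | 98.7% | 5% |
| One arm, N = 347 | 30.4 | 99.6% | 5% |
| Arms pooled, N = 584, change in intervention arm only | 18.2 | 93% | 5% |

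With factor means free, the model recovers the change of −0.349.

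**4. Sensitivity of step 3**, same formula, one arm of 237 to 347:

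- Effect of 0.28 SD: F = 0.0578, rejected 83% to 95%.
- Latent correlation 0.3: rejected 89% to 98%.
- N divided by the article's design effect of 1.7, as a rough allowance for clustering: rejected 78% to 92%.

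**5. Does correctly defined scalar invariance over time pick up a change in how intervention staff answer?** Same model, no true change, intercept shift in the intervention arm only:

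| Shift | Detected within the arm (N = 347) | Detected with arms pooled (N = 584) |
|---|---|---|
| −0.3 in 1 of 5 items | 99.7% | 94% |
| −0.2 in 1 of 5 items | 85% | 60% |
| −0.2 in 2 of 5 items | 97% | 81% |
| Same shift in all 5 items | 5% | 5% |

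The last row cannot be told apart from true change, and a between-arm intercept test could not separate it either.

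**6. Does an intercept gap between arms bias the comparison of change?** With one item intercept 0.3 higher in the intervention arm at both times, the difference in mean item change is −0.244, equal to the true 0.7 × (−0.349) = −0.244. A constant gap cancels.

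**The case against.** The best defence is that the phrase is a slip. It stands in a short recap of a separately published validation concerned with occupational groups. The same recap speaks of comparing means, so the authors evidently expect means to differ. The sentence on the trial analysis uses the usual term without repeating the faulty gloss, and an experienced analyst would probably run the standard test. This stands as to intent and lowers the likely harm. It does not make the stated rule right, and the article offers no other definition.

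Three stronger readings are tempting, and the article supports none of them.

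- A reader might infer that the plan would miss a training-induced change in how intervention staff answer. The same sentence requires scalar invariance over time, which targets that kind of intercept change, and step 5 shows that it usually finds item-specific shifts. What remains is loss of power for small shifts if the arms are pooled.
- A reader might infer that asking only for metric invariance between arms breaks the plan's own rule. It does not. The arms are compared on change, which is a comparison of effects. Metric invariance between arms plus scalar invariance over time within each arm is sufficient. A scalar requirement between arms would matter only if follow-up levels were compared.
- A reader might infer that the estimated effect would be zero by construction. The effect comes from a linear mixed model, and nothing says that an equal-means constraint carries into it.

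**Conclusion.** The point holds for the definition. Factor means do not belong in scalar invariance, and the article makes scalar invariance over time mandatory for its comparison of change. Read literally, the condition would be rejected in about 93% to 99.6% of cases when stigma falls by the planned amount, against 5% for the standard condition, and so would block the comparison the trial is designed to make.

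Those percentages rest on an assumed factor model without clustering, and on treating the planned score difference as a latent change of 0.35 SD, a mapping the article does not make. The variants in step 4 bring the figure down to 78% at the lowest. The direction follows from the definition alone. This is an error in a stated rule that should be corrected. It is not evidence that the mixed model itself is unsound.

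**What to change.** In the Quantitative data section, define scalar invariance as equal loadings and equal item intercepts (or thresholds), with factor means free. Add that invariance between the two surveys is tested within each arm. Under the assumed model, pooling the arms lowers detection of a −0.2 shift in one item, in the intervention arm only, from 85% to 60%.

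The requirement of metric invariance between arms can stay while the comparison is of change. The cost is two sentences, with no new data and no change to the mixed model.

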To the best of our knowledge—as informed by a comprehensive review of available academic literature—ours are the first research studies conducted on HIV and TB stigma among HCWs in South African healthcare facilities. Without having first established the extent and sources of HIV and TB stigma in the South African healthcare workforce, it would be premature to conduct research that compares this phenomenon in South Africa with what occurs in other countries or regions. Therefore, for our current randomised controlled trial (RCT) we chose as comparators eight randomly selected public hospitals (four intervention vs four control) situated in the same province of South Africa—the Free State (SPIRIT point 6b). This choice is sound in terms of the number of possible comparators (27 hospitals) as well as in terms of geography and expertise. The *Centre for Health Systems Research & Development (CHSR&D)* is situated at the University of the Free State (UFS) in Bloemfontein, in the middle of the province. The CHSR&D was established 25 years ago in the Faculty of the Humanities and has considerable expertise, as well as working partnerships, built over decades of research in the province’s public health facilities. The University of Antwerp (AU), Faculty of Political and Social Sciences, Department of Sociology, *Research Centre for Longitudinal & Life Course Studies (CELLO)* has a very long history of fruitful research partnership with the CHSR&D and also has excellent working knowledge of public health in the province.

In response to the research needs outlined above, as well as to extend the preliminary work of our *Stigma Score Pilot Study*, the CHSR&D and CELLO designed a randomised control trial with two key objectives (SPIRIT point 7) in mind: (1) to measure stigma by scientifically assessing the extent and sources of HIV and TB stigmatisation among the healthcare workforce and (2) to design, refine and test evidence-based, stigma-reduction interventions in randomly selected public hospitals in the Free State Province of South Africa.

This article presents the protocol for the RCT, and is written to comply with the recommended SPIRIT guidelines for RCT protocols [31] (Additional file 1).

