## Outcomes (SPIRIT point 12)

Primary outcomes:Measurement of the extent of HIV- and TB-related stigma among the public healthcare workforce in the Free State Province of South Africa, and the generation of information on the sources of such stigma.(Time points: rough estimates calculated by December 2016 to inform partners’ decision on trial continuation; Year 4, December 2018, calculate the change in the extent of stigma by comparing measures obtained in baseline statistics *with* measures generated in post-intervention survey data)Evidence-based, stigma-reduction interventions are developed and tested in randomly selected public hospitals in the Free State Province of South Africa.(Time points: start of interventions in Year 3, March 2017 to Year 4, December 2018 when quantitative data from the post-intervention survey, and the qualitative data from focus groups and interviews are generated and analysed)

Secondary outcome:

The environment in which HCWs in intervention hospitals seek care is improved.By ‘environment’ we mean, for instance, that greater awareness of HIV and TB stigma—and hopefully diminished stigma—can create a workplace that is more sensitised and empathetically responsive to human rights. We also anticipate that when staff who test and treat other staff within a facility are well supported clinically, they are likely to provide more confident and accurately tailored services. In turn, this could encourage HCWs to seek and use health services provided in the workplace, which diminishes time taken off work and should help to some extent to alleviate HCW shortages and associated pressures on other HCWs.

(Time point: Year 4, December2018, when quantitative data from the post-intervention survey, and qualitative data from focus groups and interviews are generated and analysed)

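### The planned mixed model reads as a difference in changes and names no use of the equal baseline means that randomisation gives; a common-baseline model is generally more efficient, by an amount the documents cannot fix.

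*Protocol article*

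**What the plan says.** In the protocol article, Data analyses, Quantitative data (SPIRIT point 20a; 20b), the second analysis step after follow-up is to "apply linear mixed modelling to analyse changes in HIV and TB stigma between the intervention and the control group". On the two measurements per person it adds: "The within-subject correlation between the two time points can then be accounted for by introducing a random effect into the model". This is the only random effect named. No baseline covariate or constraint on the baseline means is mentioned.

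Outcomes (SPIRIT point 12) uses the same language. For December 2018 the task is to "calculate the change in the extent of stigma by comparing measures obtained in baseline statistics" with the post-intervention measures.

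The design is a closed cohort in eight randomised hospitals, four per arm: "The same HCWs participate in baseline and the post-intervention surveys" (Sampling (SPIRIT point 14)).

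The sample size in that section compares score levels and not changes. It states "The mean stigma score considered for the control group was 0.85 with a standard deviation of 0.71", with the score expected to be "reduced by approximately 24% to 0.65 in the intervention group with a standard deviation of 0.39".

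**The concern.** When both scores are outcomes and the effect is a difference in changes, the model estimates a separate baseline mean for each arm and subtracts the baseline difference in full. Under randomisation that difference is chance alone. Full subtraction is optimal only when baseline and follow-up are perfectly correlated. At lower correlations it adds noise, and below a correlation of 0.5 it gives a less precise estimate than ignoring baseline.

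With four hospitals per arm and no more to be added, precision is scarce. The baseline data are already collected, and the choice can be settled before the 2018 follow-up survey.

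**Working it through.** **1. The plan's own figure.** From "Sampling": means 0.85 and 0.65, SDs 0.71 and 0.39, two-sided 5%, 90% power.

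n = (1.960 + 1.282)² × (0.71² + 0.39²) / 0.20² = 172.4, so 173 per arm, as stated. 173 × 1.7 = 294 against 292 stated, and 2 × 292 = 584. These figures rest on a comparison of levels and do not depend on how baseline is used.

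**2. Large-sample formulas.** Let r be the correlation between baseline and follow-up hospital means, with equal variances at both times. Relative to a follow-up-only comparison:

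- difference in changes: 2(1 − r)
- best use of a common baseline mean: 1 − r²
- ratio of the second to the first: (1 + r)/2, which is never above 1

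**3. Correlation of hospital means.** Inputs: m = 584/8 = 73 per hospital and ICC 0.05 (both from "Sampling"). The person-level correlation is assumed to be 0.5. The hospital-level correlation over time (call it CAC) is varied, because the documents give no value.

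Hospital share of the variance of a hospital mean: w = 73 × 0.05 / (1 + 72 × 0.05) = 3.65/4.6 = 0.793. Then r = w × CAC + (1 − w) × 0.5.

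**4. Eight hospitals.** The formulas in step 2 treat the correlation as known. A simulation of eight hospital means (200,000 runs per row) estimated the hospital-level variance components, held them non-negative and treated the person-level components as known. It also fitted a regression of the follow-up hospital mean on the baseline hospital mean. Entries are variances relative to the difference in changes.

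| CAC | r | Large-sample (1 + r)/2 | Common-baseline model, simulated | Hospital-mean covariate, simulated |
|---|---|---|---|---|
| 0.3 | 0.34 | 0.67 | 0.71 | 0.83 |
| 0.5 | 0.50 | 0.75 | 0.81 | 0.94 |
| 0.7 | 0.66 | 0.83 | 0.90 | 1.04 |
| 0.8 | 0.74 | 0.87 | 0.95 | 1.09 |
| 0.9 | 0.82 | 0.91 | 0.99 | 1.14 |

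With the person-level correlation varied over 0.3-0.7, the common-baseline column becomes 0.69-0.74, 0.79-0.83, 0.88-0.92, 0.93-0.96 and 0.97-1.00.

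**5. Why the covariate version differs.** Estimating its slope from eight means in two arms inflates the variance by about 1 + 1/4 = 1.25. The ratio becomes 1.25(1 + r)/2, which exceeds 1 once r > 0.6. At r = 0.66 this gives 1.04 and at r = 0.82 it gives 1.14, as simulated. The residual degrees of freedom also fall from 6 to 5.

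**The case against.** **The model is not fully specified.** The text names no arm-by-time term and no free baseline means. A mixed model with both scores as outcomes is also the framework in which a common baseline is imposed, and the full protocol (Additional file 9) is not shown. This stands in part: a constrained baseline is not excluded. But both the analysis and outcome sections speak of change, so a difference in changes is the natural reading. The point is a better choice of method, not a complaint about missing detail.

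**Few hospitals weaken the case for adjustment.** This stands against two stronger readings. A reader might infer that a change analysis is never more precise than any baseline adjustment, so that a hospital-mean covariate would serve equally well. Steps 4 and 5 show otherwise when hospital means are stable over time.

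A reader might also take power gains from the large-sample formulas. With an effect of 0.20, a pooled SD of 0.573 and 6 degrees of freedom for both analyses, these are 38% to 48%, 62% to 68% and 77% to 81% at CAC 0.5, 0.8 and 0.9. They treat the slope as known and are upper bounds. For the hospital-mean covariate with 5 degrees of freedom, simulated power at the same three values was 40%, 58% and 71%, so it falls below the change analysis at the last two.

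**Nothing stated is wrong.** This stands. Under randomisation the difference in changes is unbiased and targets the same effect as the follow-up difference. A reader might infer that the sample size is invalidated, but it claims no gain from baseline and does not depend on this choice.

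**Conclusion.** The point holds as one of efficiency. The planned analysis, on its natural reading, is valid but generally less precise than a model that uses the common baseline mean. At ICC 0.05, 73 staff per hospital and a person-level correlation of 0.5, the variance reduction is roughly 15-30% for a hospital-level correlation over time of 0.3-0.5, about 10% at 0.7, and close to nil at 0.9.

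The documents do not say where in that range the trial lies. The figures also assume equal variances in both arms and at both times, equal hospital sizes and no pairing term. The plan's SDs (0.71 and 0.39) and arm totals (347 and 237) differ, so the percentages are approximate. In the scenarios checked, the common-baseline model was no worse than the change analysis, apart from simulation noise at the top of the range. With hospital components estimated, its type I error stayed at or below about 5%.

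**What to change.** State the primary estimate as the arm difference at follow-up from a linear mixed model with:

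- both time points as outcomes;
- random effects for hospital, hospital-by-time and person;
- one baseline mean common to both arms;
- small-sample degrees of freedom suited to eight hospitals.

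Report the unconstrained difference in changes as a sensitivity analysis. Do not offer adjustment for the hospital mean baseline score as an equivalent.

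The change needs only analysis wording, settled before follow-up data are seen. It needs no extra data, participants or hospitals, and the stated sample size is untouched by it.

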## Methods/design

### Trial design (SPIRIT point 8)

The research follows a stratified cluster RCT design. Pre intervention, a self-administered questionnaire with the pilot study’s validated stigma scales was used to measure stigma and other key variables among randomly selected HCWs in all eight randomly selected sites. The intervention comprises of stigma reduction activities at three social-ecology levels (individual, community, and structural) in the four intervention sites. To evaluate implementation, an outside assessor will appraise the trial mid-way through its implementation, partly by collecting qualitative data from purposively selected HCWs. Post intervention, all respondents from baseline will be followed up using the same scales with added questions on interventions. Quantitative and qualitative data will be collected to assess the size of the impact as well as to uncover the processes through which the interventions may impact on stigmatisation.

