### Study setting and site selection (SPIRIT point 9)

The study settings are public hospitals in the Free State Province, South Africa. From the total population of 28 hospitals that could be selected as comparators, one was eliminated (Pelonomi Regional Hospital) because it was the site of the Stigma Score Pilot Study.

In order to ensure an equal distribution of large and small hospitals across the different districts in both intervention and control arms, hospitals of similar size (based on numbers of staff), and where possible in the same district, were deliberately paired. Within these pairs, a coin toss was used to randomly allocate hospitals to Arm A or Arm B, and then again to allocate the two arms to intervention or control. The number of hospitals required was estimated considering the fact that the number of staff members across the hospitals in each group differ. The average number of staff members per hospital considered is 220. The same parameters were used as those used to calculate the sample (described later), and the number of hospitals required was estimated to be approximately four hospitals per group (intervention / control). A full list of the sites appears in the addenda (Additional file 2).

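### The outcome model names a random effect for the person but none for the randomised hospital; followed as written, its type I error exceeds 5% whenever hospitals change differently over time

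*Protocol article*

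**What the plan says.** Under Trial design the article states: "The research follows a stratified cluster RCT design". Under Study setting and site selection, hospitals of similar size, and where possible of the same district, were paired. "Within these pairs, a coin toss was used to randomly allocate hospitals to Arm A or Arm B", and a second toss decided which arm received the intervention. This gives four hospitals per arm.

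Under Sampling, the sample size allows for clustering: "The coefficient of variation considered for each group is 0.25 and the intra-cluster correlation coefficient is 0.05". A design effect of 1.7 is applied to 173 per arm, which leads to 584 participants in total.

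Under Data analyses, Quantitative data, the second analysis step is a linear mixed model for changes in stigma between the arms. The only correlation it addresses is the one between a person's two measurements: "The within-subject correlation between the two time points can then be accounted for by introducing a random effect into the model". The section mentions no hospital or pair effect, no cluster-robust variance, no hospital-level test and no degrees of freedom suited to eight clusters. It then describes SEM, path and mediation models, again without hospital clustering.

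**The concern.** The unit of randomisation should be the unit of inference. A model with only a person effect compares the arms as if several hundred staff had been allocated individually, and refers the result to roughly 1.96. Only eight units were randomised, so the critical value on 6 degrees of freedom is 2.45, and on 3 (four pairs) it is 3.18.

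If staff in one hospital change together, for reasons unrelated to the intervention, a person-only model counts that shared change as many independent pieces of evidence. The standard error of the arm-by-time effect is then too small, and a chance difference between four hospitals and four others can be reported as stigma reduction. The article says that the results will go to the provincial health department with recommendations.

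**Working it through.** **Inputs from the article.** Control arm: "The mean stigma score considered for the control group was 0.85 with a standard deviation of 0.71". The score is expected to fall "to 0.65 in the intervention group with a standard deviation of 0.39", a difference of 0.20. Two-sided alpha is 0.05, power 90%, ICC 0.05 and the total 584, with four hospitals per arm. The mean number analysed per hospital is 584/8 = 73.

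**Inputs assumed, not in the article.** These are the person-level correlation between the two surveys, r, taken as 0.3 to 0.7, and the share of hospital variance that changes between surveys, d, taken as 0 to 50%. All hospitals are given 73 people, although the stated split (347 and 237) implies about 87 and 59 per hospital.

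**The plan's own figure.** n per arm = (1.960 + 1.282)² × (0.71² + 0.39²) / 0.20² = 172.4, rounded up to 173. This matches. 173 × 1.7 = 294, against the stated 292, which is close enough.

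**Type I error of the change test with a person effect only.** With two time points and complete data, this test is equivalent to a comparison of individual changes. Stable hospital and person components cancel, which leaves:

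- ICC of change = 0.05d / [0.05d + 0.95(1 − r)]
- Design effect DE = 1 + (73 − 1) × ICC of change
- Type I error = 2 × [1 − Φ(1.96/√DE)]

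Example with d = 10% and r = 0.5: ICC of change = 0.005/(0.005 + 0.475) = 0.0104; DE = 1 + 72 × 0.0104 = 1.75; type I error = 13.8%.

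| Hospital variance that changes | r = 0.3 | r = 0.5 | r = 0.7 |
|---|---|---|---|
| 0% | 5.0% | 5.0% | 5.0% |
| 5% | 8.2% | 9.5% | 12.4% |
| 10% | 11.4% | 13.8% | 19.0% |
| 20% | 17.3% | 21.4% | 29.1% |
| 50% | 30.2% | 36.1% | 45.2% |

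A simulation of change scores with 20,000 runs per setting agrees: about 5% at 0%, 11-19% at 10%, 17-29% at 20% and 31-46% at 50%. In the same simulation, a t-test on the eight hospital mean changes (6 df) rejected in 4.7% to 5.1% of runs in every setting.

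**Power once hospital is the unit (follow-up comparison, ICC 0.05, 73 per hospital).** DE = 1 + 72 × 0.05 = 4.6. Standard error = √[(0.71² + 0.39²) × 4.6 / 292] = 0.102, so the standardised effect is 0.20/0.102 = 1.97. Power is about 50% by the normal approximation, 38% on 6 df and 28% on 3 df. The 3 df figure gives pairing no credit for reducing variance.

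**The case against.** Three objections have weight.

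First, the analysis section does not exclude a hospital effect. Its sentence says what a random effect can do for repeated measures and is not a full model specification. The article is based on a longer protocol, supplied as an additional file and not shown here. A reader might infer that the plan has decided to ignore clustering, or that it contradicts its own sample size. The text supports neither: it names one source of correlation and is silent on the other. But it goes beyond leaving detail to another document. It names the model, the random effect and that effect's purpose, and an analyst who follows it literally leaves hospital out.

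Second, a reader might infer that type I error is bound to be far above 5%. The documents do not establish that. The ICC of 0.05 describes the score. Applied directly, it gives 36% (DE 4.6), but for a comparison of levels, whereas the plan tests change in the same people. If hospital effects were fully stable, the error would be exactly 5%.

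Full stability is still an unsafe assumption on the article's own account. Baseline recruitment began in February 2016 and the follow-up survey is set for 2018. In between, a national test-and-treat strategy began, and that shift together with staff shortages left two of the four intervention hospitals without a functional occupational health unit. These are hospital-specific changes, although the article does not show that they moved stigma scores.

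Third, the SEM and path models are largely exploratory. That limits what should be asked of them: hospital clustering matters there only where they estimate an intervention effect.

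**Conclusion.** The point holds in conditional form. The only random effect named in the model that tests the intervention is for the person, although hospitals were randomised and the sample size assumes that they matter. Run as written, the test has type I error above 5% whenever hospitals change differently over time. It reaches about 11-19% with 10% of the hospital variance changing, 17-29% with 20% and 30-45% with 50%.

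These figures rest on 73 people per hospital, the stated ICC of 0.05, and assumed values for the person-level correlation and for the stability of hospital effects. The omission itself is certain from the text; the size of the error is not. Modest drift is enough to more than double the nominal rate, and the correction can be made before follow-up data exist.

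**What to change.** State the primary model in full: arm, time and arm-by-time as fixed effects, persons nested in hospitals, and random effects for person, hospital and hospital-by-time. Test arm-by-time with hospital-based degrees of freedom, either by Kenward-Roger or by an analysis of hospital mean changes.

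Prespecify one primary version and report the other as a sensitivity analysis:

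- unpaired: 8 − 2 = 6 df, critical value 2.45; or
- pairs as a design term: 4 − 1 = 3 df, critical value 3.18.

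The two are not interchangeable, so the choice must be fixed before follow-up data are seen. Where SEM or path models estimate an intervention effect, use standard errors that allow for hospital clustering.

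The change is to the analysis wording, but it has a real cost. Confidence intervals widen, and power is well below the stated 90%: about 38% on 6 df or 28% on 3 df for a follow-up comparison at ICC 0.05 and 73 per hospital. Power for the change contrast depends on the same correlations that the documents do not give. The loss comes from having eight hospitals; a person-only model would merely hide it. The protocol should state this limitation alongside the revised model.
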